### Data management and monitoring

The participants will be given a unique code for identification. All data will be stored in a folder for each participant and the folder will be kept in a locked cabinet at each nursing home during study time. When the study is concluded, or the participant’s drops out, each folder will be stored according to the routines for archives of research material. After baseline and follow up assessments, the data will be registered in SPSS files at a lap-top especially designated for the OPEN study. Back up files will be created and stored. The interviews will be tape-recorded, transcribed and stored according to the routines for archives of research material.

The study is initiated and planned by the research study group with a multi-professional composition (physicians, physiotherapists, occupational therapist, nurse and dietitian).

No interim analyses of the data will be performed. The research group will have access to the final dataset. Each member of the research group will be allowed to share some of the data supervising master or PhD-students who will be involved in the analyses.

### Data analyses

All data will be entered into a database using SPSS (iBM). Quality controls will be made to check that the data are entered correctly. The baseline characteristics of the participants in the intervention and control groups will be compared using descriptive statistics. All analysis will be done by members of the research group and by an independent statistician respectively.

Data for primary and secondary outcome measures will be analysed using descriptive and comparative statistical analyses including multi-level statistics appropriate for the data measurement levels and data distributions. Data will be analysed according to intention-to-treat, i.e. participants who will drop out before completing the 12 weeks of follow up will be included in the data analysis. The model of data analysis needs to consider the effect of clustering. Thus, this study will use mixed effect models with the cluster treated as a random effect.

Combining the resource units with the cost price will allow the calculation of total costs of each group. The cost effectiveness calculation will use the EQ5D-5 L as outcome. Costs and effects will be examined based on the principle of cost-consequence analysis. This type of analysis lists all relevant costs and effects (consequences) in order to capture as much information as is feasible, in order to allow decision makers to choose the outcome of interest for inclusion in economic analyses [54].

The qualitative data consisting of tape-recorded interview-answers will be transcribed verbatim. The qualitative data sets will be analysed from a data-driven inductive approach. More specifically, the transcripts of the interviews will be read and analysed using a constant comparative method described by [29].

The analysis of the qualitative data will have a Grounded theory (GT) approach. Traditionally, GT has been applied when the ambition to capture phenomena in different social contexts have been in focus. GT is also used as a reliable technique to form theory and hypothesis in un-exploited areas. The findings from a GT study often entail facts that are valuable assets in development of assessments, creation of questionnaires and so forth in quantitative studies [29]. According to GT methodology, the analysis is performed in different steps. Initially, the interview transcripts are read through repeatedly until the researcher has a full understanding of them. Thereafter a so called line-by-line coding of the material is performed [55]. Here, significant aspects that relate to the aim of the study, and the specific foci of the research questions are marked and saved. Thereafter, the codes are sorted in a structured manner to identify trends and patterns so that they can be collected under different clusters; called categories [50]. In the final stage, the material is scrutinized from the different categories’ viewpoint to identify and let potential abstracted themes to emerge. As the analysis undergo a constant comparison process, securing that the aim of the study is held in the fore through all analytic steps, the trustworthiness of the codes, categories and themes respectively, are to be considered high [55].

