### Intervention

#### Intervention group

The intervention period will last for 12 weeks and the participants in the intervention group will perform the STS exercise, where the older person will get up from a chair to stand and then sit down again repeatedly for 1–10 times at each session depending on the participant’s ability, at least four times per day, seven days a week. The exercise will take place in conjunction with daily activities for the older person such as dressing, toileting or at transfers, and be supported by trained staff. The staff will document in a flow chart how many times per day the participant completes the activity.

The staff will be educated about the objectives of the study, and the STS exercise, at group meetings at each unit. In cooperation with the unit manager, several “key-persons” in the staff will be identified, in order to be facilitators during the intervention. The physiotherapist, occupational therapist and/or nurse working at the unit will also be asked to encourage and give practical advice to the staff regarding the STS exercise. The key-persons and representatives of the research group will meet during the intervention period. The purpose for these meetings will be to encourage the key-persons and staff to discuss problems with the intervention that might occur.

The participants will also be offered an oral protein-rich supplement (125 ml, 18 g protein which is 24% of Recommended Dietary Intake, 300 kcal) twice a day (between breakfast and lunch and in the afternoon) during 12 weeks (7 days/week). Studies indicate that only between 50 and 65% of the prescribed volume is consumed (23). Therefore, we chose a supplement with low volume and high protein content. The drink will be served in specially designed study glasses, graded in quarters. The staff will register the intake of the supplements on a flow chart designed for this purpose.

Documentation of the daily exercises and nutritional supplements will be checked every week by the key-persons.

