### Data collection/outcomes

The quantitative data will be collected at baseline and at the 12-week follow-up. An overview of the data collection is presented in Table 1. The following assessments will be performed to follow variables related to the primary and secondary aims for the study:

**Table 1 Tab1:** Participant timeline

	Enrollment	Allocation	Postallocation		
TIMEPOINT	*-t* _*1*_	0	*t* _*1*_ *baseline*	*t* _*2*_ *intervention*	*t* _*3*_ *w 13*
ENROLLMENT:					
*Eligibility screen*	X				
*Informed consent*	X				
*Information to staff and next of kin*	X				
*Identification of* *“key-persons” and meetings together with representatives from the research group*		X	X	X	X
Allocation		X			
INTERVENTIONS:					
*Sit-to-stand*				X	
*Oral supplementation*				X	
ASSESSMENTS:					
*Sit-to-stand*			X		X
*Functional balance*			X		X
*Walking ability*			X		X
*ADL*			X		X
*Nutritional status*			X	X subgroup	X
*Health related quality of life*			X		X
*Healthcare resource use*			X		X
*Demographic data*			X		
*Medical incidences*				X	X
*Interviews of residents*					X
*Interviews of staff*				X	X

t_1_ baseline, t_2_ intervention period of 12 weeks, t_3_ 12 weeks follow up

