##### Nutritional status

Mini Nutritional Assessment-Short Form (MNA-SF) will be performed [36]. MNA-SF is scored 0–14 points. It includes six parts: evaluating decline in food intake, weight loss, mobility, physiological stress or acute disease, cognitive condition and BMI or calf circumference. 12–14 = normal nutritional status; 8–11 = at risk for malnutrition; 0–7 = malnourished. Food intake will be registered 2 consecutive days at baseline, at 6- and 12-week follow-up in a subgroup (25%) of the participants in the intervention group. Blood chemistry: Plasma albumin, plasma transthyretin, plasma C-reactive protein (CRP) to determine any active inflammatory process. Further the anabolic mediator plasma insuline-like growth factor-1 (IGF-I) and D-vitamin status will be assessed by S-25 (OH) vitamin D. Body composition measurements: Bioelectrical impedance analysis (BIA) [37].

*Quality of life* will be assessed using the EQ5D-5 L [38], a questionnaire comprising 5 questions corresponding to 5 health domains: pain, mood, mobility, self-care and daily activities. Each question has 5 levels: level one = no problems, level two, three and four = some, moderate or pronounced problems and level five = extreme problems. The participants’ opinion of their own health today, is valued according to a visual analogue scale. The scale is ranged from 0 = worst imaginable health state, to 100 = best imaginable health state.

*Healthcare Resource Use* data will be assessed by The Resource Utilization in Dementia (RUD©) [39] on the key cost components including: time of the healthcare assistant for personal ADL, hospitalizations (including length of stay), the number of visits to different types of healthcare professionals (both as outpatients and as a home visit), use of lifts.

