### Data collection procedure

Residents living in Swedish NH’s today are frail and vulnerable and a rapid decrease in length of stay between 2006 and 2012 has been reported. The most dramatic change was an increase in the proportion of people who moved into an institution and died shortly afterwards [56]. This will probably result in a prolonged recruitment process to the study. A pilot study was performed at one NH with 81 residents to test the study protocol and its feasibility. Some changes were made in the protocol regarding exclusion criteria. The cut off for BMI was raised from 28 to ≤30 and Mini Mental State Examination will be used [40] to assess and describe cognitive function instead of Short Portable Mental Status Questionnaire [57].

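### Resource use is scheduled only at baseline and 12-week follow-up, so residents who die or leave in between have no planned assessment of the costs they incur during the trial

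*Protocol article*

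**What the plan says.** Under Data collection/outcomes the protocol article sets the general schedule: "The quantitative data will be collected at baseline and at the 12-week follow-up". In Table 1 the row "Healthcare resource use" carries a mark at t1 and at t3 (headed week 13) and none at t2, the intervention period. Under Intervention group the length is given: "The intervention period will last for 12 weeks".

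The Healthcare Resource Use paragraph under Secondary outcomes names the instrument: "data will be assessed by The Resource Utilization in Dementia (RUD©) [39] on the key cost components including" the time of healthcare assistants, use of lifts and, in its own words, "hospitalizations (including length of stay), the number of visits to different types of healthcare professionals". No look-back period is given.

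Data analyses then states: "Combining the resource units with the cost price will allow the calculation of total costs of each group". The same section includes participants who drop out before 12 weeks in the analysis. The Sample size calculation allows for 20% attrition among 120 residents. Data management and monitoring sends a resident's folder to the archive when that resident drops out.

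**The concern.** Admissions, bed-days and visits build up over time. A total for a group over 12 weeks needs each resident's use from baseline until the end of follow-up or until that resident's own exit. With assessments only at t1 and t3, a resident admitted to hospital in week 5 who dies in week 8 has a baseline record and nothing after it. The analysis section counts that resident in, but the collection schedule supplies nothing to count.

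The loss is unlikely to be random. The Discussion calls residents frail and says of Swedish nursing homes: "The most dramatic change was an increase in the proportion of people who moved into an institution and died shortly afterwards". Residents who are hospitalised or close to death plausibly use more care and are also less likely to reach t3. If the arms differ in attrition or hospitalisation, the cost comparison in Aim II is distorted by the very events it should register.

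This is a matter of data collection. An analysis plan can prescribe imputation, but it cannot recover admissions that nobody recorded.

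**Working it through.** **Inputs from the protocol article**
- 120 residents, 60 per group, 20% attrition over 12 weeks (Sample size calculation).
- Intervention period of 12 weeks = 84 days (Intervention group).
- Resource use at t1 and t3 only (Table 1).
- Dropouts included in the analysis (Data analyses).

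**The plan's own figure.** For a difference of 2, SD 3.5, two-sided α = 0.05 and power 0.80: n = 2 × (1.960 + 0.842)² × 3.5² / 2² = 48.1, so 49 per group, as stated. Allowing for 20% attrition, 49 / 0.80 = 61.25, so 62, and 49 × 1.20 = 58.8, so 59. The planned 60 lies between. Nothing below turns on that difference; only the 120 and the 20% are used.

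**Step 1: residents without a t3 assessment.** 0.20 × 120 = 24, or 0.20 × 60 = 12 per group if attrition is equal. The other 96 have t3.

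**Step 2: the most that t3 can cover.** Take the case most favourable to the plan: the t3 form looks back over all 84 days, so completers are fully covered.
- Against planned resident-days: (96 × 84) / (120 × 84) = 8,064 / 10,080 = 80%.
- Against days actually spent in the trial, assuming leavers stay half the period on average: 8,064 / (8,064 + 24 × 42) = 8,064 / 9,072 = 89%.

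So 11% to 20% of resident-days have no planned resource-use assessment, whatever the look-back. The share of cost would be larger than the share of days if leavers cost more per day than completers, and smaller if they cost less. The document gives no figure for this.

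**Step 3: effect on the group total.** If leavers' unrecorded use is simply not added, the total is too low, because costs cannot be negative. If their use is imputed from completers, the result is too low where leavers cost more than completers, and can be too high where death ends their costs early. If they are left out, the total describes only residents who reached t3, contrary to the stated intention-to-treat approach. The difference between arms is distorted to the extent that the number, timing or cost of exits differs between arms.

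**The case against.** The strongest reply is that two assessment dates do not mean two days of data. The listed items are retrospective counts, so a t3 form reaching back to baseline would capture the whole interval for everyone who is assessed. That stands. A reader might infer that use between the visits is lost for completers too, but the documents do not support this: the look-back is not given, and an article may leave it to the full protocol or the case report form.

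A reader might also contrast the row "Medical incidences", which is marked at t2 and t3, and conclude that continuous capture was planned for falls and ulcers but not for costs. That does not hold either. The Medical incidences section assesses those events from records at baseline and at the 12-week follow-up, so the t2 mark is weak evidence of a different method.

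Further fair points:
- The 20% is the allowance made in the sample size for the primary outcome, not a forecast of missing cost data. The 24 is therefore the plan's own working figure, not an estimate.
- The remark on early deaths is used in the article to explain slow recruitment, and residents at a terminal stage are excluded. It makes informative loss plausible but does not measure it.
- Resource data need no performance test, so staff or records could supply them for a resident who has gone. That is true, but the article plans no such step.
- Leavers keep their baseline data, and handling of missing costs may be set out in an analysis plan that is not shown. Neither supplies what they used after baseline.

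**Conclusion.** The point holds for residents who die or leave before t3, and only for them. On the stated schedule they have no planned resource-use assessment after baseline, although the analysis includes them and reports group totals. On the plan's own allowance that is about 24 of 120 residents, and 11% to 20% of resident-days even with a full 84-day look-back; the lower figure assumes that leavers stay half the period on average.

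Totals would probably be understated, because residents who are hospitalised or dying are plausibly costly and likely to miss t3. The comparison would be biased if attrition differs by arm. Both statements are reasoned expectations: the documents show neither the direction nor the size. The matter touches a secondary aim and leaves the primary outcome and the sample size alone. It should still be settled while the data can be collected.

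**What to change.** Keep the RUD at t1 and t3, and state that the t3 look-back covers the whole period since baseline. For every enrolled resident in both arms, extract hospital admissions, length of stay and professional visits from patient records from t1 until t3, death or withdrawal, whichever comes first and within the consent given. Do this in the same pass as falls and pressure ulcers, which already come from those records. Base the group totals on this extraction, and show it in Table 1 and in Data analyses.

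The cost is some extra extraction work. One limit remains: care received outside the home may be incompletely recorded in nursing home records, and this should be reported with the results.

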### Dissemination policy

Trial results will be communicated by the research group to the participating NH’s (managers, staff, residents, family members and relatives) and to the sponsors, the healthcare professionals and the public. The study will result in several different publications in peer reviewed journals.

## Discussion

### The intervention

The STS exercise has earlier been studied in different settings with promising results. The novelty with this study design is the combination of the STS exercise with protein-rich supplements. The study by Slaugther and colleagues [25] revealed that the low-intensive STS exercise for 6 months could be performed by older NH residents, and that the participants in the intervention group, to a greater extent, maintained their mobility and functional outcomes compared with the control group. If the STS exercise together with a protein-rich oral supplement results in improved muscle strength in older frail persons, it would increase their functional status and lead to greater independence in activities of daily living. The residents’ physical and mental health could be expected to improve. Even the work situation for staff would be positively affected. One innovative feature of the OPEN study is the simple intervention consisting of a basic daily activity that can be completed by several of NH residents with the support of the existing staff and actual resources. It would also be of interest if a positive result can be obtained in 3 months of intervention compared to the 6 months of intervention in the study by Slaughter et al. [25]. A positive result of our study could be important for many NH residents for the purpose to postpone physical decline and decreased independence.

A crucial point of the study design will be to educate and motivate the staff to support the residents to complete the intervention, i.e. the STS exercise and intake of oral nutritional supplement. To meet these challenges, “key-persons” at each unit in the staff will be identified and educated. The physiotherapist, occupational therapist and nurse working at the unit will also be asked to encourage and give practical advice to the staff regarding the STS exercise.

### Data collection procedure

Residents living in Swedish NH’s today are frail and vulnerable and a rapid decrease in length of stay between 2006 and 2012 has been reported. The most dramatic change was an increase in the proportion of people who moved into an institution and died shortly afterwards [56]. This will probably result in a prolonged recruitment process to the study. A pilot study was performed at one NH with 81 residents to test the study protocol and its feasibility. Some changes were made in the protocol regarding exclusion criteria. The cut off for BMI was raised from 28 to ≤30 and Mini Mental State Examination will be used [40] to assess and describe cognitive function instead of Short Portable Mental Status Questionnaire [57].

### The interviews (staff, residents)

Although there is evidence that STS exercise stabilizes older residents’ mobility no studies are, to our knowledge, published exploring the residents’ experiences or perceptions of the STS exercise, neither on staff’s experiences on supporting older persons to complete the exercises. A strength of the focus group methodology, which will be used in the interviews with the staff, is that it enables respondents to share experiences, that in turn will feed into- or trigger- the memories of others, that will be able to share more in-depth thoughts and ideas. The interviews of the residents how he/she perceived the experience of daily being offered to conduct the STS exercise and to drink the nutritional supplement (with support of staff) will be useful knowledge and valuable information for future studies.

### Healthcare resource use

Another strength of the study design is the *Healthcare Resource Use* data that will be assessed by The Resource Utilization in Dementia (RUD©) [39] on the key cost components; time of the healthcare assistant for personal ADL, hospitalizations (including length of stay), the number of visits to different types of healthcare professionals (both as outpatients and as a home visit), use of lifts. Economic aspects are important to include in intervention studies like this to encourage implementation of new routines.

In conclusion, the OPEN study design with a combination of daily basic activity and protein rich oral supplement in NH residents will add new knowledge in several aspects in this field. The effects of the multicomponent intervention regarding mobility/functional status, nutritional status and health economy will be highlighted. The presumed simplicity of the intervention will also be explored by staff and resident’s experiences.

## Abbreviations

ADL: Activity daily living
BMI: Body mass index
GT: Grounded theory
MNA-SF: Mini Nutritional Assessment – Short Form
NH: Nursing home
OPEN: Older person’s exercise and nutrition study
RUD: The Resource Utilization in Dementia
STS: Sit to stand
